## Abstract

**Background:**

Major Depressive Disorder (MDD) is among the most prevalent and disabling medical conditions worldwide. Identification of clinical and biological markers (“biomarkers”) of treatment response could personalize clinical decisions and lead to better outcomes. This paper describes the aims, design, and methods of a discovery study of biomarkers in antidepressant treatment response, conducted by the Canadian Biomarker Integration Network in Depression (CAN-BIND). The CAN-BIND research program investigates and identifies biomarkers that help to predict outcomes in patients with MDD treated with antidepressant medication. The primary objective of this initial study (known as CAN-BIND-1) is to identify individual and integrated neuroimaging, electrophysiological, molecular, and clinical predictors of response to sequential antidepressant monotherapy and adjunctive therapy in MDD.

**Methods:**

CAN-BIND-1 is a multisite initiative involving 6 academic health centres working collaboratively with other universities and research centres. In the 16-week protocol, patients with MDD are treated with a first-line antidepressant (escitalopram 10–20 mg/d) that, if clinically warranted after eight weeks, is augmented with an evidence-based, add-on medication (aripiprazole 2–10 mg/d). Comprehensive datasets are obtained using clinical rating scales; behavioural, dimensional, and functioning/quality of life measures; neurocognitive testing; genomic, genetic, and proteomic profiling from blood samples; combined structural and functional magnetic resonance imaging; and electroencephalography. De-identified data from all sites are aggregated within a secure neuroinformatics platform for data integration, management, storage, and analyses. Statistical analyses will include multivariate and machine-learning techniques to identify predictors, moderators, and mediators of treatment response.

**Discussion:**

From June 2013 to February 2015, a cohort of 134 participants (85 outpatients with MDD and 49 healthy participants) has been evaluated at baseline. The clinical characteristics of this cohort are similar to other studies of MDD. Recruitment at all sites is ongoing to a target sample of 290 participants. CAN-BIND will identify biomarkers of treatment response in MDD through extensive clinical, molecular, and imaging assessments, in order to improve treatment practice and clinical outcomes. It will also create an innovative, robust platform and database for future research.

**Trial registration:**

ClinicalTrials.gov identifier NCT01655706. Registered July 27, 2012.

## Background

Depressive disorders, including Major Depressive Disorder (MDD), are highly prevalent and disabling conditions with substantial personal and societal costs [1]. MDD is now the second leading cause of disability worldwide [2] and contributes to excess mortality associated with many comorbid medical conditions [3]. Treatment of depressive disorders is based on empirical data and evidence-based guidelines, but treatment selection remains more of an art than a science. Hence, the discovery of clinical and biological markers, or biomarkers, of treatment response that would inform an individualized approach to depression treatment remains a research goal [4].

A major challenge to identify predictors (baseline characteristics that predict response), moderators (baseline characteristics that predict differential response to a specific treatment) and mediators (events or changes occurring during treatment that explains the response) is that MDD is a complex, heterogeneous condition. A variety of neurobiological and environmental influences, both independently and in combination with one another, can alter the clinical expression of MDD in terms of symptoms, severity, episode duration, response to treatment, and functional outcomes. As a result, no single intervention is effective for all people with depression. Current diagnostic systems such as the DSM-5 [5] can reliably codify depressive symptoms as criteria for MDD, but these symptoms are not unique to depression and, even if clustered together, may not represent a specific underlying disease process or a treatment substrate. Hence, the clinical entity termed “Major Depressive Disorder” represents only the final, external manifestations of an enormously complex, multi-level, multi-factorial process.

The Canadian Biomarker Integration Network in Depression (CAN-BIND) [6] was created with an aim to use an integrated approach to biomarker discovery. CAN-BIND draws on multidisciplinary expertise from investigative teams at 8 Canadian universities, all in active collaboration with the Ontario Brain Institute (OBI) [7] and Indoc Research (Toronto, ON, Canada). The Canadian Institutes of Health Research, academic institutions, and various industry partners provide additional funding and support (see Acknowledgements).

The overall goal of CAN-BIND is to identify predictors, moderators, and mediators of treatment response and non-response in people with MDD to guide clinical decision-making. CAN-BIND-1 uses an integrated clinical, neuroimaging and molecular approach with high-dimensional mathematical modeling techniques to specifically search for (a) baseline predictors and moderators of antidepressant and adjunctive agent response, (b) early treatment mediators of response (changes from baseline to 2 weeks), and (c) later treatment mediators of response (changes from baseline to 8 weeks, and to 16 weeks).

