## Methods

### Overview of protocol

Patients with MDD are treated with open-label escitalopram 10–20 mg/d for 8 weeks. Responders (≥50 % reduction in Montgomery-Åsberg Depression Rating Scale [MADRS] score) continue on escitalopram for another 8 weeks, while non-responders have aripiprazole 2–10 mg/d added on to escitalopram for 8 weeks. Clinical, neuroimaging and molecular assessments are conducted at Baseline (Week 0) and Weeks 2 and 8; clinical and molecular assessments also are conducted at Weeks 4, 10, and 16; and additional brief clinical evaluations are completed at Weeks 6, 12, and 14. Clinical characterization assesses a broad palette of symptoms, functional outcomes, cognitive performance, personality dimensions, and recent and past life events.

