### Procedure

At the Screening Visit, eligible participants provide written, informed consent for all study procedures. Each patient undergoes screening evaluations that include a full psychiatric consultation to confirm a diagnosis of MDD using the Mini International Neuropsychiatric Interview (MINI) [8]. Previous medication history (type, dose, and duration) is collected using the Antidepressant Treatment History Form (ATHF) [9]. A detailed medical history and listing of concomitant treatments, if any, are recorded. A reproductive/menstrual history is obtained from female patients. Patients undergo medical work-up that includes physical examination, height and body weight measurements, clinical laboratory assays, and 12-lead electrocardiography (if indicated). Social background is collected using standardized reporting forms for demographic characteristics, handedness, ethnicity, education (expressed as years of formal schooling), marital status, occupational status, job classification, and household income. Participants are screened for contraindications to magnetic resonance imaging (MRI).

Figure 1 shows an overview of the protocol. At the Baseline Visit (Visit 1, Week 0), extensive clinical assessments are conducted, and blood and urine samples are obtained for molecular analysis. Participants also undergo the first of 3 sessions of structural and functional neuroimaging and electroencephalography (EEG), as described below. All patients start treatment with escitalopram and receive standardized clinical management based on the CANMAT clinical guidelines [10].

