### Treatments

In Phase 1, patients receive flexibly dosed escitalopram (10–20 mg/d) for 8 weeks. Patients are started at 10 mg/d and increased to 20 mg/d at Week 2 if they do not achieve ≥20 % reduction in MADRS score from baseline, and at Week 4 for those who do not achieve ≥50 % reduction in MADRS.

In Phase 2, patients who achieve ≥50 % reduction in baseline MADRS score at Week 8 are considered “responders” and continue on their effective dose of escitalopram for a further 8 weeks. Patients who do not achieve ≥50 % reduction in MADRS are considered “non-responders” and receive flexibly dosed aripiprazole (2–10 mg/d), added to escitalopram, for a further 8 weeks. Dose increases of aripiprazole are recommended if patients do not achieve ≥50 % reduction in MADRS after 2 or 4 weeks.

This standardized algorithm reflects usual clinical practice, is consistent with evidence-based treatment guidelines [11–13], and promotes consistency across all sites. Doses can be decreased at the discretion of the treating psychiatrist if patients do not tolerate higher doses. Treatment is open-label, and no randomization procedures are used. Medication adherence is monitored with pill counts at each visit.

Concomitant non-psychotropic medications for stable conditions are allowed at the discretion of the study psychiatrist, who can also permit use of vitamins, supplements, oral contraceptives, and non-prescription analgesics. Patients on pre-existing stable doses are allowed to continue on zopiclone up to 7.5 mg prn or lorazepam 1–2 mg prn, to a maximum of 3 doses/week.

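### CAN-BIND-1 sets out to find moderators of treatment response, but its design contains no treatment contrast that could identify them

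*Protocol article*

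**What the plan says.** The Background section separates three kinds of marker. Predictors are baseline features related to response. Mediators are changes during treatment that explain response. The third kind is "moderators (baseline characteristics that predict differential response to a specific treatment". The same section then assigns to CAN-BIND-1, by name, a search for "baseline predictors and moderators of antidepressant and adjunctive agent response". The Methods paragraph of the abstract repeats this as an analysis target: "multivariate and machine-learning techniques to identify predictors, moderators, and mediators of treatment response".

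The treatment plan is as follows.

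- **Phase 1** (Procedure): "All patients start treatment with escitalopram and receive standardized clinical management".
- **Phase 2** (Overview of protocol): responders at Week 8 stay on escitalopram, while "non-responders have aripiprazole 2–10 mg/d added on to escitalopram for 8 weeks".
- **Allocation** (Treatments): "Treatment is open-label, and no randomization procedures are used".
- **Healthy participants** (Procedure): assessed on a similar schedule but untreated.

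The primary objective in the abstract is narrower than the aim in the Background. It names "predictors of response to sequential antidepressant monotherapy and adjunctive therapy in MDD" and does not mention moderators. The Analyses section powers a comparison of responders with non-responders. It also lists, as one outcome group, Week 8 non-responders who respond by Week 16 on augmentation.

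**The concern.** On the article's own definition, a moderator is a feature-by-treatment interaction: the feature must relate to outcome differently under one treatment than under another. To see that, patients who are otherwise comparable must receive different treatments. Here treatment is constant in Phase 1 and is a fixed function of the Week 8 MADRS result in Phase 2. A stated aim therefore appears to promise something that the data cannot show.

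What is at stake is interpretation. A predictor tells a clinician how a patient is likely to fare; a moderator bears on which treatment to choose. If a feature related to outcome in this cohort were called a moderator, it would carry the second meaning with evidence only for the first. The same applies to Week 16 response after augmentation. Without concurrent non-responders kept on escitalopram alone, an effect of aripiprazole cannot be told apart from late response to escitalopram or from regression to the mean.

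**Working it through.** **1. The plan's own figures (Analyses).** Split: 0.60 × 200 = 120 responders and 200 − 120 = 80 non-responders, as stated. Sample size: with m = 25,000 features, m1 = 250 truly different, false discovery rate q = 0.05 and power 0.90, the per-test level is

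α = m1 × power × q / ((m − m1)(1 − q)) = 250 × 0.90 × 0.05 / (24,750 × 0.95) = 11.25 / 23,512.5 = 0.00048.

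The article gives no effect size. Assuming a difference of 1.0 SD, a two-sided t-test has power 0.903 at 49 per group, and 49 is the smallest number that reaches 0.90. Dividing by the Mann–Whitney efficiency, 49 / 0.955 = 51.3, rounded up to 52. Both stated minima reproduce. They concern a contrast between outcome groups, not between treatments.

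**2. Phase 1.** Write the moderator model for biomarker x and treatment T as Y = b0 + b1·x + b2·T + b3·x·T, where b3 is moderation. Every patient has T = 1, so the T column equals the intercept and the x·T column equals x. The design matrix has rank 2 of 4, and b3 cannot be separated from b1. Sample size does not enter the argument. The healthy participants do not help, since they are neither depressed nor treated. Escitalopram dose does not help either, because under Treatments it is raised according to MADRS response.

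**3. Phase 2.** Let R = 1 for Week 8 responders and A = 1 for aripiprazole. The protocol sets A = 1 − R. With columns 1, x, R, A, x·R, x·A there are two exact dependencies, R + A = 1 and x·R + x·A = x, so the rank is 4 of 6. If R is left out, a coefficient for x·A can be computed. It is then the slope in non-responders on the combination minus the slope in responders on escitalopram, and it mixes response group with treatment.

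**4. The local contrast at 50%.** A discontinuity analysis at the cut-off could in principle compare patients just on either side. A generous benchmark is a hypothetical 1:1 randomised comparison in all 200 patients. The detectable difference in slope is (z for α + z for power) × 2 / √N, in outcome SD per biomarker SD.

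- One test, two-sided 0.05, 80% power: (1.960 + 0.842) × 2 / √200 = 0.40.
- At α = 0.00048 and 90% power: 0.68.

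A discontinuity analysis relies on the patients near the cut-off and would do worse than this.

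**5. Threshold crossing by noise (illustration).** The assumptions, none given in the article, are that Week 16 response is referenced to Week 0, that true severity does not change after Week 8, and that the within-patient SD s is 2 to 4 points. Take baseline MADRS 30, so the cut-off is 15.

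| Week 8 score | Formula | s = 2 | s = 3 | s = 4 |
|---|---|---|---|---|
| 16 (47% reduction) | Φ(−1/s) | 31% | 37% | 40% |
| 20 (33% reduction) | Φ(−5/s) | 0.6% | – | 10.6% |

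The Treatments section ties response to baseline explicitly only at Week 8. If Week 16 response were instead referenced to Week 8, the patient at 16 would need a score of 8 or less, and Φ(−8/s) is 0.003% (s = 2) to 2.3% (s = 4).

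**The case against.** The best defence is that little of the plan depends on the word. The primary objective names predictors, the powered analysis compares outcome groups, and the later modelling is described as prognostic. No moderator test or sample size is stated. The article calls this a discovery study, and its Discussion leaves other interventions to later protocols. All of that is right, and it limits the reach of the point. It does not remove the point, because the Background assigns moderators to CAN-BIND-1 itself and defines the term.

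A second defence is the local contrast at the 50% cut-off. It stands in principle for aripiprazole, so a flat statement that moderation of the adjunct can never be examined would go too far. No such analysis is described, it would be weak, and it offers nothing for escitalopram.

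A reader might also infer more than the article supports:

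- **That prognostic features will be reported as moderators and used to select treatment.** No section says so. Nor need the naive Phase 2 interaction be falsely positive. In one simulated setting with 200 patients, a biomarker correlated 0.4 with Week 8 reduction and the same aripiprazole effect for everyone, it was rejected in 5.0% of 4,000 runs at the 5% level. The difficulty is what the coefficient means.
- **That power for moderation equals α.** If the term cannot be estimated there is no test, and power is undefined.
- **That 31% to 40% of augmentation responses are noise.** That range describes one borderline patient. The article gives no Week 8 distribution from which an overall share could be derived.
- **That the augmentation outcome group is itself a claim of an aripiprazole effect.** As written it describes a course under a regimen. The caution concerns how it is interpreted.

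**Conclusion.** The point holds for the moderator part of the baseline aim and for its repetition in the abstract. For escitalopram, moderation is not identifiable at any sample size. For aripiprazole it is fully aliased with Week 8 response, with only an unplanned and weak local contrast left. This follows from the article's own definition and allocation rule and needs no outside figure; it assumes that the Phase 2 rule is followed as written. The predictor aims, the primary objective, and the 120/80 split with its minima of 49 and 52 per category are untouched.

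The interpretive caution about Week 16 response on augmentation also holds. Its size is not known: the borderline range rests on the assumed Week 0 reference and the assumed SD, and falls quickly away from the cut-off.

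**What to change.** Remove moderators from the CAN-BIND-1 aims in the Background and from the analysis statement in the abstract, or reserve them explicitly for later protocols that include comparator treatments. State that CAN-BIND-1 identifies predictors of outcome under open-label escitalopram and, in Week 8 non-responders, under escitalopram plus aripiprazole. In the Analyses section, say that Week 16 response in the augmented group is outcome during the combined regimen and is not specific to aripiprazole.

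Routine adjustment of Phase 2 analyses for Week 8 MADRS is not part of this fix. It would change the estimand and would not restore moderation, so the choice can stay with the analysis plan.

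The change is one of wording. It alters no treatment, visit, endpoint or sample size. The cost is a narrower claim.

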## Methods

### Overview of protocol

Patients with MDD are treated with open-label escitalopram 10–20 mg/d for 8 weeks. Responders (≥50 % reduction in Montgomery-Åsberg Depression Rating Scale [MADRS] score) continue on escitalopram for another 8 weeks, while non-responders have aripiprazole 2–10 mg/d added on to escitalopram for 8 weeks. Clinical, neuroimaging and molecular assessments are conducted at Baseline (Week 0) and Weeks 2 and 8; clinical and molecular assessments also are conducted at Weeks 4, 10, and 16; and additional brief clinical evaluations are completed at Weeks 6, 12, and 14. Clinical characterization assesses a broad palette of symptoms, functional outcomes, cognitive performance, personality dimensions, and recent and past life events.

### Participants

Participants are recruited at 6 clinical centres: Vancouver (Djavad Mowafaghian Centre for Brain Health), Calgary (Hotchkiss Brain Institute), Toronto (2 sites: University Health Network and Centre for Addiction and Mental Health), Hamilton (St. Joseph’s Healthcare Hamilton), and Kingston (Providence Care, Mental Health Services). Research Ethics Boards at each site approved the study. Recruitment draws upon outpatient-referral networks, community-based advertising, and dedicated knowledge translation (KT) activities.

Table 1 lists the inclusion and exclusion criteria for the patients with MDD. Healthy comparison participants are 18–60 years of age, with no psychiatric or unstable medical diagnosis, and sufficient fluency in English to complete study procedures. They are matched to the patient group by sex and age distribution.

**Table 1 Tab1:** Inclusion and exclusion criteria for patients

*Inclusion Criteria*	
• Outpatients 18 to 60 years of age.	
• DSM-IV-TR criteria for MDE in MDD, as confirmed by the MINI.	
• Depressive episode duration ≥3 months.	
• Free of psychotropic medications for at least 5 half-lives (i.e. 1 week for most antidepressants, 5 weeks for fluoxetine) before baseline.	
• Score ≥24 on the MADRS.	
• Fluent in English, sufficient to complete the interviews and self-report questionnaires.	
*Exclusion Criteria*	
• Diagnosis of Bipolar I or Bipolar II disorder.	
• Any other psychiatric diagnosis that is considered the primary diagnosis.	
• Any significant personality disorder diagnosis (e.g., borderline, antisocial) that might interfere with participation in the protocol, defined by clinician judgment.	
• High suicidal risk, defined by clinician judgment.	
• Substance dependence/abuse in the past 6 months.	
• Significant neurological disorders, head trauma, or other unstable medical conditions.	
• Pregnant or breastfeeding.	
• Psychosis in the current episode.	
• High risk for hypomanic switch (i.e., history of antidepressant-induced hypomania).	
• Failed 4 or more adequate pharmacologic interventions (as determined by the ATHF).	
• Previously failed or showed intolerance to escitalopram or aripiprazole.	
• Started psychological treatment within the past 3 months with the intent of continuing treatment.	
• Contraindications to MRI.	

DSM-IV-TR, Diagnostic and Statistical Manual of Mental Disorders, Fourth Edition, Text Revision; MDE, Major Depressive Episode; MDD, Major Depressive Disorder; MINI, Mini International Neuropsychiatric Interview; MADRS, Montgomery-Åsberg Depression Rating Scale; ATHF, Antidepressant Treatment History Form

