### Analyses

We will examine several outcomes, including responders at Week 8 who maintained response at Week 16, responders at Week 8 who are non-responders at Week 16, non-responders at Week 8 who respond at Week 16 with augmentation, and non-responders at Weeks 8 and 16, among other outcomes. A reasonably large dataset is required to study adequately the complex clinical, neuroimaging, and molecular factors that contribute to treatment outcomes. Our sample size target for this phase of the CAN-BIND program is 200 patients and 90 healthy participants (290 in total).

To identify standalone features that differ significantly between responders and non-responders, either at baseline or over the course of the study, parametric two-sample t-tests will be used for features with normally distributed data. Otherwise, the non-parametric Mann–Whitney *U* test will be used. A significance threshold of α = 0.05 and multiple testing corrections will be required. Given an input list of up to 25,000 features, of which at least 250 are differentially expressed between responders and non-responders, assuming an overall false discovery rate of 5 %, and applying two-sample t-testing procedures, a minimum of 49 subjects per category are required for power of at least 90 % to correctly identify a given feature which differs significantly between the categories. If nonparametric testing procedures are used, a minimum of 52 subjects per category are required to achieve the same power. Target recruitment for patients with MDD is 200. An estimated response rate of 60 % would yield 120 responders and 80 non-responders. The planned sample size is sufficiently powered for both parametric and non-parametric univariate testing. Multivariate analysis and the development of prognostic signatures of escitalopram response will follow univariate analysis.

Data analyses will be conducted using a suite of commercial and open-source software tools installed on high-end workstations at HPCVL. While data from each analytical platform will be independently analyzed using the methods described above, important relationships (either correlational or causal) between modalities can be detected through an integration of data collected across assessment platforms for a given study subject.

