## Progress to date

Between 2013 and 2015, 159 participants (107 patients and 52 healthy participants) were screened and 134 (85 patients and 49 healthy participants) entered at baseline in the initial protocol with the Emotional Face Categorization/Conflict Task during MRI and EEG sessions, as noted above. Full neuroimaging data (to Week 8) were obtained from 71 patients and 45 healthy participants.

Table 3 lists the clinical characteristics of this first cohort (*N* = 134) that were evaluable at baseline. Independent-samples t-tests showed no significant demographic differences between patients and healthy participants. The patients were moderately depressed at baseline, as reflected by MADRS, QIDS-SR, and CGI-S mean scores, as well as moderately impaired as assessed by psychosocial (SDS) and work (LEAPS) functioning scales.

**Table 3 Tab3:** Clinical characteristics of the first cohort (*N* = 134)

Characteristic	Patients with MDD (*N* = 85)	Healthy participants (*N* = 49)
Female:Male, *N* (%)	50:35 (59 %:41 %)	32:17 (65 %:35 %)
Age in years, mean (SD), range	36.1 (12.5), 19–61	32.5 (10.2), 20–57
Ethnicity^a^, *N* (%)		
Aboriginal	0	0
Arab	3 (4 %)	1 (2 %)
Asian	9 (11 %)	9 (18 %)
Black	1 (1 %)	0
Latin American/Hispanic	5 (6 %)	2 (4 %)
White	59 (69 %)	35 (71 %)
Other	5 (6 %)	2 (4 %)
Mixed	3 (4 %)	0
Marital status, *N* (%)		
Never Married	48 (57 %)	26 (53 %)
Separated	7 (8 %)	1 (2 %)
Married	16 (19 %)	12 (25 %)
Divorced	7 (8 %)	3 (6 %)
Domestic Partnership	5 (6 %)	6 (12 %)
Widowed	2 (2 %)	1 (2 %)
Occupational status, *N* (%)		
Working now	45 (53 %)	28 (57 %)
Disabled (permanent or temporary)	13 (7 %)	0
Temporary leave	5 (3 %)	0
Looking, unemployed	10 (5 %)	3 (6 %)
Student	8 (4 %)	15 (31 %)
Retired	1 (1 %)	0
If employed, number of hours scheduled to work over the past 2 weeks: mean (SD)	50.0 (27.2)	53.8 (25.8)
If employed, number of hours missed due to symptoms over the past 2 weeks: mean (SD)	10.5 (18.2)	0.1 (0.6)
Education, years: mean (SD)	14.1 (2.0)	15.9 (2.9)
Age of onset of MDD, years:		
mean (SD), range	20.6 (10.7), 5–55	n/a
Single episode:Recurrent, *N* (%)	24:61 (29 %:71 %)	n/a
No. previous episodes, mean (SD)	4.3 (2.8)	n/a
Current episode duration		
≤12 months	39 (46 %)	n/a
1–2 years	13 (15 %)	
>2 years	30 (35 %)	
Unknown/not reported	3 (4 %)	
Median duration (range), months	14.5 (3–151)	
Comorbidities^b,c^		
Substance-Related Disorders	7 (8 %)	n/a
Anxiety Disorders	67 (79 %)	
Eating Disorders	1 (1 %)	
Stable medical conditions	52 (61 %)	

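### The responder v non-responder feature tests cannot hold age or sex constant: the stated power is met, but an adjusted test would detect more and would screen out features that only track age or sex

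*Protocol article*

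**What the plan says.** Table 1 (Participants) admits "Outpatients 18 to 60 years of age". In the first cohort (Table 3, Progress to date) patient age has mean, SD and range "36.1 (12.5), 19–61", and 50 of 85 patients are women (59%).

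The only control for age and sex in the article concerns the healthy participants: "They are matched to the patient group by sex and age distribution". Under Treatments, the article states that treatment is open-label and not randomised. Response groups are formed by outcome.

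The Analyses section fixes the test used to find features that separate the two response groups: "either at baseline or over the course of the study, parametric two-sample t-tests will be used for features with normally distributed data". It continues: "Otherwise, the non-parametric Mann–Whitney *U* test will be used". On error control it says: "A significance threshold of α = 0.05 and multiple testing corrections will be required". The sample size rests on these same tests: 49 subjects per category (t-test) or 52 (nonparametric) for at least 90% power at a 5% false discovery rate (FDR), against an expected 120 responders and 80 non-responders. The section then says that each platform's data will be analysed independently by these methods, and that multivariate analysis and prognostic signatures follow the univariate step.

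**The concern.** Age and sex are plausible sources of variation in imaging, EEG and molecular features. The plan balances the healthy group on exactly these two variables but does nothing comparable for responders and non-responders, the contrast on which the study is sized. A two-sample t-test or Mann–Whitney test leaves two things uncontrolled.

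- **Precision.** Whatever part of a feature's variance is due to age and sex stays in the error term, so smaller differences are harder to detect than they need be.
- **Interpretation.** If response is related to age or sex, a feature that merely tracks either one does differ between the groups. FDR control limits chance findings and does not remove this kind of hit. The search starts without preselected biomarkers, so no prior hypothesis would filter out such proxies.

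A marker that only restates age or sex would not help the stated goal of guiding clinical decisions.

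**Working it through.** **Inputs from the article.** 25,000 features, of which 250 truly differ; FDR 5%; power 90%; 49 or 52 per category; 120 v 80 expected; patient age SD 12.5 years.

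**Assumptions (not in the article).** Two-sided tests; a standardised difference d; R², the share of within-group feature variance explained by age and sex; the age gap between response groups; and the correlation of a feature with age.

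**Step 1: reproduce the plan's figure.** The per-test level implied by the FDR is

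α* = 250 × 0.9 × 0.05 / (24,750 × 0.95) = 0.000478.

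With the noncentral t distribution and d = 1 SD, 49 v 49 gives 90.3% power. The nonparametric figure follows from the asymptotic relative efficiency: 49 / 0.955 = 51.3, rounded up to 52. Both stated numbers reproduce, with an effect of 1 SD that the article does not state.

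**Step 2: unadjusted power at the planned size.** The noncentrality is d × √(120 × 80 / 200) = 6.93d.

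- d = 1.0: 99.96%
- d = 0.7: 90%
- d = 0.5: 47%

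The stated target is therefore met with a wide margin.

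**Step 3: power with age and sex in the model.** Adjustment replaces d by d / √(1 − R²) and uses two fewer degrees of freedom.

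| R² | d = 0.5 becomes | Power, d = 0.5 | Power, d = 0.7 |
|---|---|---|---|
| 0 (unadjusted) | 0.500 | 47% | 90% |
| 0.10 | 0.527 | 54% | 94% |
| 0.20 | 0.559 | 63% | 97% |
| 0.30 | 0.598 | 72% | 99% |

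This takes age and sex as unrelated to response. If the groups differ by 5 years (0.4 SD), the variance of the adjusted estimate grows by a factor of about 1 + 0.24 × 0.4² = 1.04, where 0.24 = 0.6 × 0.4 is the product of the group shares. The gain shrinks slightly.

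**Step 4: features linked to response only through age.** The induced difference is d = correlation × gap / 12.5. The chance of passing α* at 120 v 80, unadjusted, is:

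| Age gap | Correlation | Induced d | Per-test rate | Multiple of 0.048% |
|---|---|---|---|---|
| none | any | 0 | 0.048% | 1 |
| 3 years | 0.5 | 0.12 | 0.38% | 7.9 |
| 5 years | 0.5 | 0.20 | 1.7% | 35 |

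Sex can act in the same way. If 65% of responders and 50% of non-responders were women and a feature differed by 1 SD between the sexes, the rate would be about 0.5%.

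**The case against.** The strongest reply is that the tests named are only a first screen of standalone features. Multivariate work follows, and a master Statistical Analysis Plan, not shown here, could add covariates or test features already residualised for age and sex. That is fair as far as it goes, and the missing covariate list is not held against the article. But the article does name the tests, sizes the study on them and applies them to every platform. An adjusted screen would have to replace or rework what is written.

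Three further objections stand and limit the point.

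- **Power.** A reader might infer that ignoring age and sex leaves the study short of its minimum of 49 per category. The documents do not support this. The 49 was derived for an unadjusted test, the smaller expected group has 80, and power at the reproduced 1 SD effect is 99.96%.
- **Confounding.** A reader might infer that the unadjusted tests will produce false biomarkers. That requires age or sex to differ between responders and non-responders, and the article reports no such comparison. The 3.6-year gap in Table 3 (36.1 v 32.5) is between patients and healthy participants, which is a different contrast. Without an association with response, the unadjusted tests keep their nominal error rate. Nor should the risk be quoted at an uncorrected 5% level, because the plan requires multiple-testing correction.
- **Prediction.** The article defines predictors as baseline characteristics that predict response. An age-linked feature can meet that definition, so barring every feature that fails after adjustment from the signatures would go too far.

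For features defined as change from baseline, differencing within patients already removes stable age and sex effects on level, so R² is likely to be lower there.

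**Conclusion.** The point holds as an inefficient and avoidable choice of test, not as an error in the sample size or a demonstrated bias. The fault lies in the Analyses section; the age criterion itself is sound. The article's 90% power claim is met.

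Relative to an adjusted analysis, the loss is about 7 to 25 percentage points of power at d = 0.5 (47% against 54–72%) and about 4 to 9 points at d = 0.7, if R² is 0.10 to 0.30. It is negligible at d = 1. The interpretive risk is conditional: with an assumed age gap of 3 to 5 years and a correlation of 0.5, the per-test rate for a feature that only tracks age is about 0.4 to 1.7% instead of 0.048%. R², the gap and the correlation are all assumptions, as the article gives none of them. The change is worth making because it is nearly free.

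**What to change.** In the Analyses section, make the primary per-feature test a linear model of the feature on response status with age (continuous) and sex as covariates, and a rank-based version for features that are not normally distributed. Apply the same 5% FDR to the adjusted p-values. Report the unadjusted t-test or Mann–Whitney result alongside. Judge the prognostic signatures by what they add to age and sex, with no rule that only adjusted associations may enter them.

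The cost is a change of wording, two degrees of freedom and no new data, since both variables are already recorded. The one drawback is that features whose predictive value runs through age or sex will rank lower in the screen; the unadjusted results keep them visible. The wording should be settled before the response groups are analysed.
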